### Data collection

After obtaining consent, research assistants will collect all baseline participant data. Because of low literacy and education levels of participants, all questionnaire assessments will be interviewer administered in Spanish by native Spanish speakers. Research assistants will also collect all anthropometric and clinical measures, including: height, weight, waist circumference, blood pressure (BP), HbA1c, and cholesterol. Research assistants will be trained by professional medical staff. Data collection will take place concurrently for control and intervention arms.

### Data management and security

All study data collected will be entered by UCD research staff using double-data entry. Data will be stored and managed using Research Electronic Data Capture (REDCap) tools hosted by the Biomedical Informatics Program of the UCD Clinical and Translational Science Center. REDCap is a secure, web-based application designed to support data capture for research studies [27].

Hard copies of the consent forms and any contact information and data collected will be kept in a locked, secure file only accessible to the study personnel. All electronic data related to recruitment, tracking of study subjects and associated study data will be stored and managed on secured, central servers and accessible only by password to permitted users. Such electronic information will not contain any identifiers. Data will be monitored regularly by the data manager for completeness. This study does not pose more than minimal risk to subjects as it is based on a behavioral intervention. We will follow the data monitoring plan outlined in the Data Safety Monitoring Plan submitted to the National Institute of Diabetes and Digestive Kidney Diseases (NIDDK), the primary funder. Study status reports will be submitted quarterly to the NIDDK. Any report on adverse events submitted to NIDDK will also be submitted to the UCD IRB.

### Primary outcome measures and processes

Primary outcome measures are percent changes in weight and BMI. Weight will be taken on a digital scale and measured in kilograms with participants dressed in light clothing and without shoes. Standing height will be measured with a stadiometer. Weight and height will be assessed at each data collection point, as illustrated in the Standard Protocol Items: Recommendations for interventional trials (SPIRIT) (Table 3) (check list as an Additional file 1).

**Table 3 Tab3:** Standard Protocol Items: Recommendations for Interventional Trials (SPIRIT)

	Allocation	Study period						
		Enrollment			Close-out			
Timepoint	−t_1_ − 0	0	*Baseline (t* _*0*_ *)*	Intervention (12 weeks)	*3-month FU* *(t* _*1*_ *)*	*6-month FU* *(t* _*2*_ *)*	*1-year FU* *(t* _*3*_ *)*	*1.5-year FU* *(t* _*4*_ *)*
Enrollment:								
Allocation	X							
Eligibility screen		X						
Medical clearance (if applicable)		X						
Informed consent			X					
Intervention:								
*PASOS Intervention*				X				
*Control group*				X				
Assessments:								
Background / Demographics			X		X^a^		X^a^	
Acculturation			X					
Medical history			X		X^a^		X^a^	
Clinical measures			X		X	X	X	X
*Blood pressure*			X		X	X	X	X
*Height*			X		X	X	X	X
*Weight*			X		X	X	X	X
*Waist circumference*			X		X	X	X	X
*HbA1c*			X		X		X	
*Cholesterol*			X		X		X	
Knowledge			X		X		X	
Nutrition			X		X		X	
Eating habits			X		X		X	
Smoking habits			X		X^a^		X^a^	
Alcohol consumption			X		X^a^		X^a^	
Physical activity			X		X		X	
Income			X					
Health perception			X		X		X	
Program satisfaction					X			

^a^Modified for follow-up

### Secondary outcome measures and processes

#### Clinical/anthropometric

Secondary clinical outcomes include changes in clinical measures of HbA1c, total cholesterol (TC), High-density lipoprotein cholesterol (HDL-C), BP, and waist circumference. HbA1c will be measured with the DCA Vantage™ (Siemens Medical Diagnostic Solutions, Puteaux, France), a point-of-care (POC) immunoassay analyzer that measures the percent concentration of HbA1c in blood. Lipid measurements, including TC and HDL-C, will be analyzed using the Cholestech LDX® System (Cholestech Corporation, Hayward, CA). Both of these POC testing devices have been utilized in population-based community settings and produced accurate and reproducible results as compared to “gold-standard” laboratory measures [28, 29]. BP will be measured in standard fashion, following procedures developed by the American Heart Association and taken using an automated device that employs standardized Doppler procedures. Waist circumference will be measured using a Gulick II anthropometric tape measure. HbA1c, TC and HDL-C will be measured pre-intervention, post-intervention and at the 1-year follow-up. During the baseline clinical testing, individuals who have an HbA1c of ≥6.5% will be tested a second time. If both tests are ≥6.5%, they will be referred to RAC’s clinic (*FreSalud*) and will not be eligible to participate in the study.

#### Sociodemographic data

Sociodemographic data including gender, age, race/ethnicity, marital status, level of education, years in U.S., first language learned, income, job title, and health perception will be collected at baseline. Any changes to marital status and/or job title will be collected at the post-intervention and 1-year follow-up.

#### Acculturation

Acculturation is measured using the short acculturation scale that was derived from a longer 12 item acculturation scale. This 5-item scale has shown validity and reliability as compared to other published scales [30].

#### Medical history and eating habits

Questions regarding a participant’s medical history were adapted from questionnaires used as part of the Coronary Artery Risk Development in Young Adults (CARDIA) study [31].

#### Knowledge

Questions regarding a participant’s knowledge about fruit and vegetable serving size, physical activity and water intake were adapted from the questionnaire used during the *Pasos Saludables* pilot study [23].

#### Nutrition

Questions about nutrition, including fat, fruit and vegetable intake will be asked. The questions for this section were derived from the Block Food Frequency questionnaire (FFQ) (Block Questionnaire – 2005 FFQ Spanish Version) available online. These screeners have good validity and reliability results [32].

#### Fast food, water intake and food security

Questions about the participant’s fast food and water intake as well as food security were adapted from questionnaires used in a longitudinal study that was conducted in Mendota, California with hired farm worker families [33].

#### Smoking habits and alcoholic beverage consumption

Participants will be asked two questions each regarding their smoking and alcoholic beverage consumption habits. These questions were adapted from surveys used by the Global Tobacco Surveillance System and the Behavioral Risk Factor Surveillance System respectively [34, 35].

#### Physical activity

Participants will be asked to answer questions regarding their physical activity over the previous 7 days. Physical activity questions will be divided into moderate and vigorous activities. The questions for this section were derived from the short European Prospective Investigation into Cancer and Nutrition (EPIC)-Norfolk Physical Activity Questionnaire 2 (EPAQ2) [36].

### Process evaluation

In order to assess recruitment and retention strategies, we will develop and implement process evaluation strategies that will include; tracking sign-up and enrollment rates, screening outcomes, and attendance at educational sessions and other program events. In addition, we will review participant self-evaluation and satisfaction with sessions as well as review feedback from participants given to research assistants and *promotores*. Successful completion will enable the development of a set of best practices for intervention dissemination.

Process evaluation data will come from several sources, including data on participant attendance at intervention sessions and supplemental activity events. Participants will be asked five satisfaction questions, included in the follow-up questionnaire. These questions will provide information on participants’ satisfaction with the sessions overall as well as the effectiveness of the trainer and activities. These questions will only be asked once. For most participants this will happen in the post-intervention questionnaire. For those participants who cannot be reached for this appointment, we will include the questions in their 1-year follow-up questionnaire.

### Economic evaluation

In order to evaluate the cost implications of the intervention, we will examine the intervention’s economic sustainability by analyzing productivity, injury rates, absenteeism, and health care utilization relative to the cost of the intervention. We hypothesize that the associated economic gains to the farming operation will outweigh the cost of the intervention. We will also assess the cost of implementing the intervention relative to the health benefit achieved by participants. Findings from this aim will be disseminated to other farms for consideration of possible program adoption.

Data will consist of the costs of the intervention to individual ranches and RAC. Such costs include direct program costs, net of the costs of conducting the research – costs which would not be duplicated in a commercial setting. Second, we will use data collected and maintained by RAC on overall health care costs and worker’s compensation costs for participating ranches. These data will allow for comparison between intervention and control ranches. We anticipate that participation rates in the study will vary by ranch and this will be accounted for in analysis. Third, we will utilize worker productivity data provided by RAC for participating ranches and compare across level of program participation. Productivity includes output per worker (harvesting rates, transplanting rates and other measures that might be available) as well as absenteeism. The final step is to use accounting data supplied by ranches to place benefit measures on the indicators of productivity gain. All data collected for the economic evaluation will be de-identified.

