### Preliminary data from pilot study

In 2010, University of California, Davis (UCD) collaborated with Reiter Affiliated Companies (RAC), the largest fresh multi-berry producer in the world, growing Driscoll’s proprietary varieties of strawberries, raspberries, blueberries, and blackberries year round in the US, and other international locations, on a pilot study [23]. In this randomized controlled study, 254 participants were allocated to either the control or intervention group in a 1:2 ratio for control:intervention. Farmworkers employed by RAC participated in a 10-week diabetes and obesity prevention program developed by UC Davis and delivered in Spanish by *promotores*. The majority of participants were born in Mexico and identified Spanish as their native language. Primary outcomes included change in weight, body mass index (BMI), waist circumference, and fasting blood glucose concentration. Secondary outcomes assessed changes in diet and physical activity. The pilot found small but significant reductions in weight, BMI and waist circumference in participants completing the program; the decreases were statistically significant in women, but not in men. Improvement in knowledge of healthy eating such as the number of recommended servings of fruits and vegetables, how much water to drink and how much to exercise per day was also seen. Self-reported behaviors related to a healthy lifestyle also changed in the positive direction. Participants who completed the program reported increased physical activity as well as changing their eating habits, such as eating more fruit and less fast food, drinking more water and fewer sweetened drinks. Participant retention was high, with 70% overall remaining in the study from baseline to post-intervention [23]. After the successful completion of the pilot study, we aim to implement and evaluate the effectiveness of the program on a larger scale by recruiting more participants and with a longer follow-up period. The central hypotheses of this project are that a lifestyle intervention delivered at the agricultural worksite will reduce obesity and diabetes risk for employees and will prove to be cost effective for the employer.

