**Fig. 1 Fig1:**
[figure not shown]
Study design

As part of this study, process evaluation strategies will also be reviewed. Qualitative and quantitative methods will be implemented to improve and maintain participation in the program and assess participant satisfaction. Process evaluation will continue throughout the length of the study to provide ongoing data and evaluation to guide the intervention.

We will also conduct an economic evaluation on the ranches offering the program relative to the control ranches. The objective is to document the commercial viability of ongoing programs in the berry industry and perhaps more widely among other agricultural industries as well as other industries that employ largely immigrant populations. In addition, we will evaluate the cost of the intervention relative to the health benefit achieved by participants. This analysis will exclude costs of administering the evaluation of the study but will include all costs associated with the delivery of the intervention itself. This study protocol was approved by the University of California, Davis, Office of Research, Institutional Review Board Administration (#575576).

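### The only contrast named for productivity and absenteeism is by level of voluntary program participation, so self-selection could be counted as economic gain

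*Protocol article*

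**What the plan says.** In the protocol article, the pilot study section gives as part of the central hypotheses that the intervention "will prove to be cost effective for the employer". The Study design section sets the general contrast for the economic work: "We will also conduct an economic evaluation on the ranches offering the program relative to the control ranches".

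The Economic evaluation section restates the hypothesis, "We hypothesize that the associated economic gains to the farming operation will outweigh the cost of the intervention", and gives the method as "analyzing productivity, injury rates, absenteeism, and health care utilization relative to the cost of the intervention". It then takes the company's data streams in turn:

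- Health care and workers' compensation costs: "These data will allow for comparison between intervention and control ranches".
- Productivity: "we will utilize worker productivity data provided by RAC for participating ranches and compare across level of program participation".
- What productivity covers: "Productivity includes output per worker (harvesting rates, transplanting rates and other measures that might be available) as well as absenteeism".
- What is done with the result: "The final step is to use accounting data supplied by ranches to place benefit measures on the indicators of productivity gain".

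The Statistical analysis plan section states a modified intention-to-treat basis in which effects are assessed whatever the adherence. It also says that worker productivity is combined with accounting data to give the overall economic cost or gain.

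**The concern.** Ranches are randomised; level of participation is not. The Supplemental activities section says that taking part in any study activity is voluntary, so participation level arises after randomisation and is chosen by the worker. Workers who are healthier, more reliable or more productive to begin with may attend more. A comparison across participation levels would then show higher output among high participants even if the program did nothing.

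For absenteeism the link is more direct. The Intervention section places core sessions at the ranch, in a meal break during the working day. A worker who is absent that day cannot attend. If participation means attendance, absenteeism helps to determine the exposure against which it is compared.

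At stake is the benefit side of the employer's cost calculation. The productivity contrast is the one converted to money, and the Economic evaluation section says that the findings will go to other farms considering adoption.

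**Working it through.** **Setting the sections side by side**

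| Item | Contrast named | Section |
|---|---|---|
| Economic evaluation as a whole | Program versus control ranches | Study design |
| Health care and compensation costs | Intervention versus control ranches | Economic evaluation |
| Output per worker and absenteeism | Across level of participation | Economic evaluation |
| Analyses generally | Effects irrespective of adherence | Statistical analysis plan |

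The third row differs from the other three. It is also the row that feeds the valuation step.

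**Two readings of participation level**

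The term is not defined.

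1. Worker attendance: self-selected, and for absenteeism partly set by the outcome.
2. Ranch uptake: an average of voluntary decisions, still not randomised, although the direct link between one worker's absence and attendance is weaker.

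Control ranches might be included at level zero under either reading. Only a pure comparison of arms is free of voluntary uptake.

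**Illustration of size**

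The plan gives no figure for the productivity analysis, so there is none to reproduce. The correlation r between attendance and underlying productivity is an assumption, and so is the split of attendance at its median. Both variables are taken as standard normal, with no true program effect.

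- Mean productivity of the upper half of attendance = r × √(2/π) = 0.798r; of the lower half, −0.798r.
- Upper minus lower = 1.596r. For r = 0.1, 0.2, 0.3 this is 0.16, 0.32, 0.48 SD.
- Upper half minus all controls = 0.798r, which is 0.08, 0.16, 0.24 SD.

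A simulation used 4,000 runs and 300 workers per arm (half of the planned maximum of 600), with two-sided t-tests at 5% and clustering ignored:

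| r (assumed) | Upper − lower half, SD | False positives | Upper half − controls, SD | False positives | Randomised arms, SD | False positives |
|---|---|---|---|---|---|---|
| 0 | 0.00 | 5.6% | 0.00 | 5.0% | 0.00 | 5.1% |
| 0.1 | 0.16 | 29% | 0.08 | 12% | 0.00 | 5.2% |
| 0.2 | 0.32 | 80% | 0.16 | 36% | 0.00 | 4.2% |
| 0.3 | 0.48 | 99% | 0.24 | 66% | 0.00 | 5.1% |

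The arm comparison is unbiased at every r. The participation comparison is unbiased only at r = 0. These are differences in level. If change from a pre-program period were analysed, stable differences between workers would largely cancel and the bias would be smaller.

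**The case against.** The strongest reply is that the Study design section governs. It sets program against control ranches for the whole economic evaluation, and nothing in the Economic evaluation section withdraws this for productivity. Participation level may be a further breakdown within that comparison. A reader might infer that the randomised comparison has been abandoned for productivity. The documents do not say so, and that part of the reply stands. What remains is that the section giving the method names one productivity contrast, and it is not the randomised one.

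Three further points have force:

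- Participation level could mean ranch uptake. The article says, just before the productivity sentence, that participation rates will vary by ranch and that this will be allowed for. The argument about absent workers then weakens. But no method is given, and the remark does not deal with self-selection.
- The magnitude rests on an assumed correlation and an invented split, and it concerns levels, whereas the article speaks of gain. This stands, so the figures are illustrative only.
- A reader might infer that the whole employer hypothesis rests on a non-randomised contrast. It does not: health care and compensation costs are compared by arm, and injury rates and health care utilization are also listed.

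The plea that a condensed article leaves such matters to a fuller plan does not answer the point. The contrast is stated, and it conflicts with other sections.

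**Conclusion.** The point holds as an inconsistency with a real risk of bias. Followed as written, the Economic evaluation section would give a self-selected productivity and absenteeism estimate and put a monetary value on it, while other sections promise a comparison of ranches and effects irrespective of adherence.

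The size cannot be derived from the documents. Over assumed correlations from 0 to 0.3, the spurious difference between halves of attendance runs from 0 to about 0.48 SD in level, and would be less for change. It would be too strong to say that self-selection will be read as economic gain; the documents support only that it could be. The primary outcomes, weight and BMI, are not affected. The change should be made because the affected quantity enters the test of a central hypothesis.

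**What to change.** In the Economic evaluation section:

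1. State that the main contrast for productivity and absenteeism is intervention versus control ranches as randomised, with ranch as the cluster, in line with the clinical model in the Statistical analysis plan section.
2. State that this estimate is the one entered in the cost/gain calculation.
3. Adjust for pre-program productivity where company records allow. The article does not say whether such records exist.
4. Define level of participation (worker attendance or ranch uptake, and how control ranches are placed), and label that comparison exploratory.

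The main contrast needs only a change of wording, since the company productivity data are already to be supplied for participating ranches. The price is wider intervals, because the comparison rests on about six ranches.

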### Statistical analysis plan

Analyses will use a modified intent-to-treat basis to assess the effects of the intervention regardless of adherence [37, 38]. Data collected for the primary outcome will be analyzed and summarized by standard descriptive statistics. We will analyze continuous outcomes (body weight and BMI change from baseline to end of follow-up and between intervention and control) using the mixed effects model accounting for ranch as a cluster variable. Control of other important covariates such as gender, baseline weight/BMI may be made in sensitivity analyses. Analysis of secondary outcomes will be conducted in a similar fashion. In these analyses, we will estimate ICC and report them along with other design characteristics including cluster size and number of clusters. We will not adjust for multiple testing in the analysis of the primary outcome (weight and BMI, which are virtually a single outcome as height does not change), but clearly report the analyses of secondary outcomes as secondary in publication. No interim analyses will be conducted.

Data collected to address economic evaluation, including intervention costs, health outcomes and medical costs, and worker productivity will be combined with accounting data to assess the overall economic cost/gain of the intervention. Accounting data will be compared to costs produced by the UCD Department of Agricultural and Resource Economics, which does not include costs of obesity program interventions, but does provide guidance on related issues. For example, a ranch benefits economically if a worker’s harvesting rate improves because overall harvest cost falls when worker productivity improves. Moreover, absenteeism adds uncertainty and cost of maintaining a larger workforce for equivalent production.

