**Methods:**

PASOS is an obesity and diabetes intervention program that will be implemented on ranches where immigrant farmworkers spend a considerable amount of time each day. This cluster randomized controlled study will enroll approximately 600 farmworkers. Using a uniform distribution for random number generation, ranches are randomized using a 1:1 ratio as either control or intervention. Baseline data will be taken from eligible participants and analyzed against data collected at the post-intervention, 6-month, 1-year, and 1.5-year follow-ups. The enrollment period is 1.5 years.

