## Methods

### Study design

A cluster randomized trial (CRT) design is being used to evaluate the effectiveness of a worksite lifestyle intervention in producing changes in factors known to increase risk of obesity and diabetes [23]. Ranches allocated to the intervention group will receive the worksite intervention program over 6–12 weeks. Ranches allocated to the control group will receive no intervention but will be given the opportunity to attend other educational sessions, topics covered will not be the same as those covered in the intervention program and may include such topics as communication and conflict resolution specifically geared towards farm workers. The study period is 5 years. Recruitment and enrollment of subjects is expected to take 2 years. Recruitment at ranches will be staggered so that as work crews have a sufficient number of interested participants and baseline assessments are completed, the educational sessions will begin on designated ranches. A subject’s participation in the study will begin with their consent and end after a 1.5-year follow-up data collection point, or at an earlier date if they choose to withdraw from the study (Fig. 1).

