### Study population

All potential subjects are seasonal, immigrant farmworkers with low income and education levels. Workers interested in participating in the study must meet the following inclusion criteria (1) work at Reiter Brothers, Inc. (RBI), a partner or affiliate company, (2) be at least 18, (3) plan to stay in the area for the next 3 months, (4) be willing to attend weekly sessions for the length of the educational sessions, and (5) be able to speak Spanish and to read well enough in Spanish to follow basic instructions. Exclusion criteria is as follows, (1) workers without Spanish language comprehension, (2) pregnant women and those planning a pregnancy within 6 months, (3) women who are breastfeeding, unless discontinuing breastfeeding within 1 month, (4) individuals who, without health care provider approval, are: unable to undertake moderate physical exercise, taking medicine for high blood pressure or heart conditions, have bone or joint problems, lose consciousness or fall due to dizziness, or have developed chest pain within the last month, (5) individuals taking medications that affect weight, (6) individuals with therapeutic diets, (7) previous diabetes diagnosis disclosed during screening or diabetic status determined by Hemoglobin A1c (HbA1c) testing with levels ≥6.5% who will be referred to the clinic for medical attention, (8) individuals with a spouse/cohabitant already enrolled in the study, and (9) individuals who have previously participated in *Sembrando Salud* (RAC version of PASOS) within the last 4 years.

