#### Intervention

UCD, in collaboration with RAC, developed a program by integrating aspects of several programs to create a culturally tailored curriculum appropriate for delivery in an agricultural setting. The program was designed to educate participants about obesity, diabetes and healthy lifestyles, motivate changes in their current diet habits, and provide a supportive participatory group setting. Core principles of *Salud para su Corazon*, developed by the U.S. National Heart, Blood and Lung Institute (NHLBI) are complemented with *5 Pasos*, being implemented in Mexico by the Mexican Government [24, 25]. These two programs are used synergistically to implement the goals of the intervention. Because of the simplicity of its message, *5 Pasos* provides the general framework for the program. The five steps are: 1) Move, 2) Drink water, 3) Eat fruits and vegetables, 4) Measure (food portions and weight), and 5) Share (information learned and healthy habits). The *Salud para su Corazon* curriculum is a user-friendly, bilingual program for *promotores* developed by NHLBI specifically for Latino communities. The *Salud* curriculum will be used to supplement some of the visual aids used during the delivery of the intervention program. The intervention will be implemented on farms where workers spend a considerable amount of time every day. The intervention will be delivered over 6–12 weeks and the length of follow-up will be 1 or 1.5 years depending on when the worker was enrolled in the study.

The core intervention program will consist of 12 lessons (Table 1). In order to maximize participation and retention in this group which averages long work hours, the core intervention sessions will take place at the ranch during a meal break during work hours. Sessions will be presented to work crews in a format analogous to tailgate trainings. Tailgate trainings are gatherings of small groups of workers around the tailgate of a truck, in the field, or other spot for a brief, informal and focused training session on a single topic.

**Table 1 Tab1:** PASOS Curriculum

Session	Topic
1	Introduction to PASOS and the five steps toward a healthy lifestyle
2	Understanding the importance of having a healthy heart
3	Body mass index
4	Understanding blood pressure and keeping it within healthy levels
5	Learning about diabetes
6	Understanding diabetes and side effects
7	Understanding cholesterol and keeping it within healthy levels
8	Children and overweight

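### The primary analysis reads as one baseline-to-end change per worker, so workers without a final weight drop out and the interim weights do not enter the primary contrast; no single primary visit is fixed

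*Protocol article*

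**What the plan says.** All of the following is in the protocol article.

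- **Statistical analysis plan:** the continuous primary outcomes are analysed as "change from baseline to end of follow-up and between intervention and control) using the mixed effects model accounting for ranch as a cluster variable". Ranch is the only grouping level named; no visit term or within-worker term appears. The same paragraph promises a modified intent-to-treat analysis that holds whatever a worker's adherence.
- **Primary outcome measures and processes:** "Primary outcome measures are percent changes in weight and BMI", with no time point. The same section adds: "Weight and height will be assessed at each data collection point". Table 3 puts weight at baseline, 3 months, 6 months, 1 year and 1.5 years.
- **Abstract, Methods:** baseline data will be "analyzed against data collected at the post-intervention, 6-month, 1-year, and 1.5-year follow-ups".
- **Length of follow-up:** the Intervention section says "the length of follow-up will be 1 or 1.5 years depending on when the worker was enrolled in the study". Retention puts the final follow-up at 1.5 years. Study design ends participation after the 1.5-year visit "or at an earlier date if they choose to withdraw from the study".
- **Likely loss:** workers are seasonal, and inclusion asks only that they "plan to stay in the area for the next 3 months". The pilot, a 10-week programme, ended "with 70% overall remaining in the study from baseline to post-intervention".

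**The concern.** A single change score needs both a baseline and a final weight. A worker who has left by the end therefore falls out of a comparison meant to hold regardless of adherence, even if they were weighed at 3, 6 and 12 months. Those weights are the best evidence on how the leavers were doing.

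What is at stake is mainly bias. Participants and data collectors are unblinded, and only one arm is being taught about weight. If intervention workers who are not losing weight leave more often, the final-change comparison flatters the programme. The Retention section also describes removal for attending fewer than three sessions in the context of the intervention sessions, so loss may differ by arm.

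The end point itself is also unsettled. With follow-up of either 1 or 1.5 years, the end of follow-up is not the same visit for every worker.

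**Working it through.** **1. Inputs from the article.** Up to 600 workers, at least six ranches, about 100 per ranch, 1:1 allocation; difference 3 points, SD 5 points; ICC up to 0.05; pilot retention 70% to post-intervention. The 3-point, SD-5 scenario reproduces the article's own individual-randomisation figure: a two-sided t-test at 5% with 80% power needs 44.6, so 45, per group, or 90 in total. The article gives no retention figure for 18 months.

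**2. Who has a usable interim weight.** Carry the pilot's 70% to month 3 and assume nobody returns. Then 0.30 × 600 = 180 workers have no follow-up weight at all. Those with an interim weight but no final one number 600 × (0.70 − 18-month retention):

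| Assumed 18-month retention | No final weight | Of these, with an interim weight |
|---|---|---|
| 70% | 180 | 0 |
| 60% | 240 | 60 |
| 50% | 300 | 120 |
| 40% | 360 | 180 |

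A longitudinal model recovers information only from the last column.

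**3. Bias.** Large-sample simulation without ranch effects. Assumptions: changes at 3 and 18 months are bivariate normal, SD 5, correlation 0.6 or 0.8; means 0 (control) and −3 (intervention); 70% are seen at month 3 at random. Later loss is random in controls. In the intervention arm each SD of poorer 3-month change raises the log-odds of leaving by 0.5 or 1.0. The true difference is 3.0.

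| 18-month retention | Final change only | Model also using the 3-month weight |
|---|---|---|
| 60% | 3.2 to 3.5 | about 3.0 |
| 50% | 3.4 to 4.0 | about 3.0 |
| 40% | 3.6 to 4.4 | about 3.0 |

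The overstatement runs from (3.2 − 3)/3 = 7% to (4.4 − 3)/3 = 47%. With the log-odds slope set to 0, both estimates are 3.0.

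**4. Precision, with ranch effects.** Take three ranches per arm, 300 workers per arm and ICC 0.05, with non-informative loss.

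- Ranch part of the variance of the difference: 2 × (0.05 × 25)/3 = 0.833.
- Individual part, final change only: 2 × 23.75/n18, where 23.75 = 0.95 × 25 and n18 is the number per arm with a final weight.
- Individual part, with the 3-month weight: 2 × 23.75 × [(1 − r²)/n18 + r²/n3], where r is the correlation and n3 = 0.70 × 300 = 210.

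At 60% retention and r = 0.6 (n18 = 180), the individual part falls from 0.264 to 0.250. The total SE goes from √1.097 = 1.047 to √1.084 = 1.041, a 0.6% reduction. At 40% and r = 0.8 (n18 = 120), it falls from 0.396 to 0.287. The SE goes from √1.229 = 1.109 to √1.121 = 1.059, a 4.5% reduction. The gain is therefore about 1-5%.

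**5. Power.** With six ranches, ICC 0.05 and a 3-point difference, having 420 instead of 600 workers scored lowers power from 85.4% to 83.0% (normal approximation), or from 62.3% to 59.6% (t-test on 4 df). The number of ranches dominates.

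**The case against.** The strongest reply is that the article condenses a fuller plan. The baseline-to-end wording could describe the span of data in a longitudinal model, the abstract says every follow-up is compared with baseline, and visit terms and missing-data rules commonly sit in an analysis plan not shown here. Part of this stands: the absence of a missing-data rule is no finding. But the abstract names no joint model and no primary visit, and the analysis section names only a change and a ranch effect. What is stated therefore points to one change score and leaves the primary visit open.

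Stronger readings are tempting but unsupported:

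- A reader might infer that at least 30% of workers will be unscored. The 70% is retention to the end of a 10-week pilot, so it is not a floor on loss at 18 months in this trial. The Process evaluation section expects some who miss the post-intervention visit to be reached at 1 year, and postcards, at least ten calls and larger late incentives are planned.
- A reader might infer that those same 30% have interim weights going to waste. Workers permanently lost before month 3 have none (step 2, first row).
- A reader might state as fact that interim weights are never analysed, or that the last observed weight is carried forward. The abstract contradicts the first, and nothing in the article says the second.

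The bias figures are also assumption-driven. No passage gives the retention, the correlations or the intervention-only dependence. The longitudinal model returns 3.0 because loss was made to depend on the observed 3-month change. The simulation does not cover workers removed for low attendance, who may have no post-baseline weight.

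**Conclusion.** The point holds in limited form. As most naturally read, the primary analysis discards workers without a final weight and leaves their interim weights out of the primary contrast. The article also fixes no single primary visit, because its sections disagree on 1 versus 1.5 years.

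The possible overstatement is about 0.2 to 1.4 points on a true 3, given 40-60% retention at 18 months and loss that depends on early weight change in the intervention arm only. It is zero if loss is non-informative. The precision gain is small, about 1-5% of the total standard error at ICC 0.05, and the power loss from 30% attrition is a few points at most in the case checked. The reason to change is protection against bias at almost no cost. Confidence is medium, since the wording admits a second reading and the size rests on assumed retention.

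**What to change.** In the Statistical analysis plan section:

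1. State the primary analysis as a longitudinal mixed model for weight (and likewise BMI). Use baseline and all scheduled follow-up values from every consented worker found eligible at baseline, with arm-by-visit terms, within-worker correlation and ranch as the cluster.
2. Name one fixed visit for the primary contrast, and reconcile the follow-up length in the Intervention and Retention sections with it. If the 1.5-year visit is chosen while some workers are followed for only 1 year, say that their final value is missing by design. Align the abstract.
3. Add one pre-stated sensitivity analysis for workers with no post-baseline weight, whom the model cannot recover. Examples are assuming no change from baseline in the intervention arm, or a tipping-point shift.

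**Cost:** revised wording and some extra modelling. The weights are already scheduled and the article reports follow-up as ongoing, so no new visits, staff or participants are needed. The small downside is that the model assumes loss depends on observed weights. The sensitivity analysis addresses this only for workers with no post-baseline weight; a tipping-point version could be extended to later leavers.
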